## Abstract

**Introduction:**

Physical activity is strongly recommended for youth with type 1 diabetes, yet many children and adolescents do not meet current exercise guidelines, partly because of fear of hypoglycemia. Resistance training may offer metabolic and musculoskeletal benefits, but its implementation in routine pediatric diabetes care remains limited. Diactive-1 is an mHealth program designed to deliver tailored resistance-training sessions combined with glucose-management educational support. This multicenter trial aims to evaluate the effectiveness of Diactive-1 (v2.0) in improving hangrip strength in children and adolescents with type 1 diabetes.

**Methods:**

This study is a 12-week, parallel-group, multicenter randomized controlled trial conducted across 11 Spanish pediatric endocrinology units. The target sample size is 158 children and adolescents aged 10–18 years with type 1 diabetes, with 79 participants allocated to each group. Participants will be randomized to either the Diactive-1 intervention or usual clinical care. The intervention group will use the Diactive-1 (v2.0) app, which provides individualized resistance-training programs, glucose-related educational prompts, safety thresholds for exercise, and engagement strategies such as gamification. The primary outcome will be the change in age- and sex-standardized handgrip strength z-score from baseline to 12 weeks. Secondary outcomes will include glycemic stability, insulin requirements, cardiometabolic markers, physical literacy, quality of life, psychological well-being, app usability, and intervention engagement. Analyses will follow the intention-to-treat principle using mixed-effects models.

**Expected outcomes and discussion:**

This trial will assess whether a scalable mHealth-supported resistance-training program can improve muscular strength and support diabetes self-management in routine pediatric care. By testing Diactive-1 across multiple hospitals and real-world settings, the study will provide evidence on the external validity, feasibility, and potential clinical integration of digitally supported exercise education for youth with type 1 diabetes.

**Ethics and dissemination:**

Ethical approval was granted by the Research Ethics Committee for Medicinal Products of the Government of Navarra. Written informed consent will be obtained from parents or legal guardians, with age-appropriate assent from minors. Findings will be disseminated through scientific conferences, peer-reviewed publications, and summaries shared with participating families.

**Clinical Trial Registration:**

https://clinicaltrials.gov/study/NCT07290868, identifier NCT07290868.

## Introduction

1

In 2024, the incidence of type 1 diabetes mellitus, a disease caused by immune-mediated destruction of pancreatic β-cells leading to a lack of endogenous insulin production (1), reached 219,000 new cases among children and adolescents worldwide (2), with a rate of 14.07 per 100,000 (3). This condition results in elevated blood glucose levels, known as hyperglycemia, which over time increases the risk of both macrovascular and microvascular complications (4). Indeed, it is estimated that 1 in 10 youth already exhibit microvascular impairments (5), although other complications, such as loss of muscle mass and function, should also be considered (6). Beyond the physical domain, young individuals face daily self-management demands related to type 1 diabetes management that may compromise emotional health (7). Therefore, daily diabetes care warrants close attention, as glycemic stability may have implications even for quality of life (8).

The primary therapy for type 1 diabetes is exogenous insulin administration; however, this approach is imperfect, as it contributes to the risk of hypoglycemia, defined as low blood glucose levels (9). Therefore, non-pharmacological strategies that support safe self-management in youth with type 1 diabetes should also be considered (10). Among these, physical exercise is recognized as a safe and effective adjunctive strategy for optimizing type 1 diabetes management (11). In particular, resistance training is clinically relevant because muscle-strengthening activities are recommended for children and adolescents with type 1 diabetes, yet this modality remains less studied than aerobic exercise (12). Despite the benefits of exercise, youth with type 1 diabetes tend to be more sedentary than their apparently healthy peers (13), with one of the primary barriers being fear of hypoglycemia (14). However, the literature suggests that this concern may partly reflect inadequate insulin dose adjustments around exercise rather than exercise intensity itself (15). Recent technological advances, including continuous glucose monitoring (CGM) and increasingly flexible insulin delivery systems, may help improve glycemic stability while reducing the burden of self-management (16, 17). Nevertheless, the interaction between these technologies and exercise requires careful consideration; accordingly, recent guidelines address glycemic management using CGM and automated insulin delivery (AID) systems in the context of exercise (18, 19).

In the 2026 Standards of Care in Diabetes, the American Diabetes Association (ADA) continues to recommend ≥60 minutes per day of moderate-to-vigorous physical activity and ≥3 days per week of muscle-strengthening activities for children and adolescents, recognizing exercise for the first time as an effective therapeutic strategy (20). However, a key challenge lies in enabling youth with type 1 diabetes to translate guideline-based recommendations into daily practice while understanding their individual glycemic responses to exercise. To address this gap, Diactive-1 was developed as an mHealth tool that leverages the widespread use of smartphones worldwide (21) to deliver tailored resistance training programs, responding to the limited evidence on the isolated effects of this modality (22), while incorporating glycemic monitoring around exercise to provide evidence-based recommendations (18). Our previous randomized clinical trial (RCT) conducted in Navarre, Spain, involving 62 youth with type 1 diabetes showed high usability of Diactive-1, with a score of 4.33 out of 5.00 (23), and demonstrated that participants allocated to the intervention group maintained glycemic stability while achieving significant reductions in daily insulin dose at 12 and 24 weeks compared with usual clinical care, with no reported hypoglycemic events (10). These benefits were accompanied by improvements in muscular strength, lean mass, and bone mineral content (24). Thus, Diactive-1 may have potential as an adjunctive tool to standard treatment by empowering youth to optimize daily type 1 diabetes management. However, the initial RCT was conducted in a single clinical context with a limited sample size, and the effectiveness of Diactive-1 across other hospital settings and clinical workflows remains uncertain. This could be addressed by scaling up Diactive-1 across multiple hospitals, incorporating an updated algorithm, refining the training program, and enhancing usability to promote greater engagement. Therefore, the primary aim of this multicenter randomized controlled trial is to evaluate the effectiveness of Diactive-1 (v2.0) in improving handgrip strength in children and adolescents with type 1 diabetes. Secondary aims are to examine its effects on glycemic stability, insulin requirements, cardiometabolic markers, physical literacy, quality of life, psychological well-being, and app-related engagement outcomes.

## Materials and methods

2

### Trial design

2.1

This study is designed as a 12-week, parallel-group (i.e., intervention group and usual clinical care group), multicenter RCT conducted across eleven pediatric endocrinology units in Spanish hospitals: *Universitario de Navarra* (Pamplona, Navarra), *Universitario Marqués de Valdecilla* (Santander, Cantabria), *Cabueñes* (Gijón, Asturias), *Universitario Central de Asturias* (Oviedo, Asturias), *Universitario de Cruces* (Barakaldo, País Vasco), *Universitario Araba* (Vitoria-Gasteiz, País Vasco), *San Millán-San Pedro* (Logroño, La Rioja), *General San Jorge* (Huesca, Aragón), *de Barbastro* (Barbastro, Aragón), *Clínico Universitario Lozano de Blesa* (Zaragoza, Aragón), and *Universitario Miguel Servet* (Zaragoza, Aragón). The central coordinating site for the project will be *Navarrabiomed* Biomedical Research Center (Pamplona, Navarra) from which the current RCT has been registered on ClinicalTrials.gov (Reg. ID: NCT07290868). This protocol has been developed in accordance with the Standard Protocol Items: Recommendations for Interventional Trials (SPIRIT) statement for RCT protocols (25).

### Study setting

2.2

The RCT will be conducted in a hybrid setting combining routine clinical care in hospital-based pediatric endocrinology outpatient clinics with real-world daily environments. Baseline and post-intervention assessments will be performed during routine outpatient visits by healthcare professionals trained in standardized assessment procedures, and data will be recorded through the Diactive-1 clinical web-based platform. The 12-week duration is supported by preliminary Diactive-1 findings showing relevant effects within this timeframe (10, 24). The intervention will be delivered through the Diactive-1 mHealth app in participants’ daily environments, distinguishing it from usual clinical care.

The project was initially approved by the Medical Research Ethics Committee of Navarra (PS_2025/5), approved on March 25, 2025, and has undergone additional review by the ethics committees of each hospital. The study will adhere to the ethical guidelines of the Declaration of Helsinki, the Singapore Statement, and the Oviedo Convention on Human Rights and Biomedicine.

### Eligibility criteria

2.3

This study will include children and adolescents aged 10 to 18 years with a diagnosis of type 1 diabetes mellitus of at least 6 months’ duration, with insulin requirements >0.5 U/kg/day and HbA1c >6% (26). Additional inclusion criteria are: (i) current treatment with multiple daily injections (MDI) or insulin pump therapy; (ii) use of CGM; (iii) availability to participate in the study using the Diactive-1 mHealth application; (iv) provision of written informed consent authorizing participation, signed by both the participants and their legal guardians; and (v) ability to understand Spanish or English, the languages supported by the application. Exclusion criteria are: (i) presence of comorbidities that limit the ability to perform physical activity during the study period; (ii) lack of access to a compatible device, either personal or loaned, with Android or iOS operating systems on which the Diactive-1 application can be installed; and (iii) lack of internet connectivity at the time of application use, including Wi-Fi, mobile data, or international roaming.

### Sample size and recruitment

2.4

Based on preliminary 12-week intervention data from the previous Diactive-1 trial, the between-group difference in handgrip strength z-score was 0.24 units, corresponding to an approximate standardized effect size of Cohen’s d = 0.56 (10). Using G*Power for an independent-samples comparison with a two-sided α = 0.05, 134 evaluable participants (67 per group) would provide 89.6% power, rounded to approximately 90% (27). After allowing for an anticipated attrition rate of 15%, the recruitment target was set at 158 children and adolescents in total, with 79 participants allocated to the intervention group and 79 to the usual-care group (28). Sampling will be extended until the end of the recruitment period, incorporating as many participants as possible.

Because participants will be individually randomized within hospitals, this is not a cluster-randomized trial. Nevertheless, hospital-level effects will be accounted for in the planned mixed-effects analyses by including hospital as a random effect. As the actual hospital-level ICC is not yet known, a conservative *a priori* sensitivity analysis was conducted using the design effect DE = 1+(m−1)×ICC. Assuming a mean hospital size of approximately 14.5 participants and 15% attrition, ICC values of 0.01, 0.02, and 0.05 corresponded to effective sample sizes of approximately 120, 107, and 81 participants, with estimated powers of approximately 86%, 82%, and 70%, respectively. Thus, the planned recruitment is expected to retain more than 80% power under hospital-level ICC values of up to 0.02, whereas greater clustering would result in reduced power. Recruitment may continue beyond the target sample until the end of the prespecified recruitment period.

Recruitment will take place during outpatient visits in the pediatric endocrinology units of the participating hospitals, where healthcare professionals will inform eligible participants about the study protocol, assessments, the importance of randomization, and the potential risks and benefits, in accordance with the participant information sheet. Written informed consent will subsequently be obtained, with one copy retained by the healthcare staff in a physical file and another provided to the participants or their legal guardians. All individuals meeting the inclusion criteria will be eligible to participate to minimize selection bias, with enrollment continuing until the target sample size is reached and potentially exceeded through September 30, 2026.

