### Randomization, allocation concealment, and blinding

2.5

The randomization sequence assigning participants to the study groups (i.e., exercise intervention group and usual care wait-list control group) will be generated by a computerized algorithm with no human access and implemented via the centralized Diactive-1 web-based platform. The algorithm will use a non-stratified randomization scheme with small, randomly varying even block sizes (i.e., 2, 4, 6, and 8 participants). Each block will contain an equal allocation ratio between the two groups (50%–50%), with the order of assignments within each block randomly permuted, thereby ensuring balance between groups throughout recruitment while minimizing predictability of the sequence. Because recruitment per hospital may vary, randomization will be centralized and non-stratified, with hospital-level clustering accounted for in the mixed-effects models. To ensure allocation concealment, randomization will be automatically performed after completion of the baseline clinical visit and entry of the corresponding clinical data, before the 7-day diabetes-related data-collection period.

Participants and healthcare professionals cannot be blinded due to the nature of the intervention. Outcome processing and statistical analyses will be performed using coded group allocation whenever feasible. The statistical analyst will remain blinded to group identity until the primary analyses have been completed. All hospitals and participants registered on the Diactive-1 web-based platform will be coded using alphanumeric identifiers.

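### The hospital-clustering sensitivity analysis uses the cluster-randomised design effect, so its reduced powers do not describe this individually randomised trial

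*Protocol article*

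**What the plan says.** All of the figures are in section 2.4 of the protocol article.

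- Basis: "the between-group difference in handgrip strength z-score was 0.24 units, corresponding to an approximate standardized effect size of Cohen’s d = 0.56".
- Main calculation: "Using G*Power for an independent-samples comparison with a two-sided α = 0.05, 134 evaluable participants (67 per group) would provide 89.6% power".
- Recruitment target: "After allowing for an anticipated attrition rate of 15%, the recruitment target was set at 158 children and adolescents in total".
- Design: "Because participants will be individually randomized within hospitals, this is not a cluster-randomized trial".
- Sensitivity analysis: the hospital ICC is said to be unknown, so an analysis described as conservative is run with DE = 1+(m−1)×ICC, a mean hospital size of 14.5 and 15% attrition. The result is that "ICC values of 0.01, 0.02, and 0.05 corresponded to effective sample sizes of approximately 120, 107, and 81 participants", with powers of about 86%, 82% and 70%.
- Conclusion: a trial of this size should "retain more than 80% power under hospital-level ICC values of up to 0.02, whereas greater clustering would result in reduced power".

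Two other sections bear on this. Section 2.5 sets central 1:1 randomisation in permuted blocks of 2 to 8, not stratified by hospital. Section 2.15 takes the treatment effect from the group × time interaction in a mixed model. Its random terms are intercepts for hospital and for participant within hospital, with no treatment-by-hospital term.

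**The concern.** The factor 1+(m−1)×ICC is the variance inflation when every participant in a hospital receives the same arm, so that hospital differences are mixed into the arm difference. In this trial each hospital contributes to both arms. The same paragraph says the trial is not cluster-randomised and then draws a power conclusion from the cluster-randomised formula.

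What is at stake is the published description of the trial's power. A figure of 70% at ICC 0.05 and a threshold at ICC 0.02 invite a later reader to attribute a null result to hospital clustering, which this design does not support. They also draw attention away from the quantity between hospitals that could cost power, namely variation of the treatment effect itself.

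**Working it through.** **Inputs.** Two-sided α = 0.05, d = 0.56, 67 per group, 15% attrition, m = 14.5 and ICC 0.01/0.02/0.05 (section 2.4); 11 hospitals (section 2.1); non-stratified 1:1 blocks of 2, 4, 6 and 8 (section 2.5); group × time effect with random intercepts only (section 2.15).

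**1. Main figure reproduced.** A two-sample t test with 67 per group and d = 0.56 has 89.6% power (non-central t). 134/0.85 = 157.6, hence 158. Both agree with the plan.

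**2. Sensitivity figures reproduced.** DE = 1 + 13.5×ICC = 1.135, 1.27 and 1.675. Evaluable N = 14.5×11×0.85 = 135.6. Dividing gives 119.4, 106.8 and 80.9, with t-test powers of 85.9%, 81.8% and 70.1%. Starting from a rounded 136 gives 119.8, 107.1 and 81.2. The stated 120/107/81 and 86/82/70% are therefore correct for the formula used.

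**3. The formula for this design.** Let the outcome have total variance σ², a share ICC of it between hospitals, and a treatment effect common to all hospitals.

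- Whole hospitals allocated: variance of the arm difference = (4σ²/N)×[1+(m−1)×ICC].
- Individuals allocated, arms balanced within each hospital: the hospital term is in both arm means and cancels, leaving (4σ²/N)×(1−ICC).
- Individuals allocated without stratification, hospital ignored: balance holds only on average, and the variance is about 4σ²/N.

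So the applicable factor lies between about 1−ICC and about 1. With 1−ICC, the effective N is 134/0.99 = 135.4, 134/0.98 = 136.7 and 134/0.95 = 141.1, with powers of 89.9%, 90.2% and 91.0%.

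**4. Simulation of the design** (134 evaluable, 11 hospitals, non-stratified allocation, d = 0.56, 8,000 runs per ICC, ICC placed on the analysed outcome itself):

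| ICC | Plan | t test ignoring hospital | Random hospital intercept |
|---|---|---|---|
| 0 | 89.6% | 89.5% | 89.5% |
| 0.01 | 86% | 89.8% | 89.7% |
| 0.02 | 82% | 89.0% | 89.1% |
| 0.05 | 70% | 90.0% | 90.6% |
| 0.10 | – | 89.7% | 91.3% |

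The Monte Carlo standard error is about 0.3 points (√(0.9×0.1/8000)). Unequal hospital sizes at ICC 0.05 gave 90.1% and 90.6%. Fixed hospital effects, which the plan does not use, cost about 2 points at low ICC (87.3% at 0.01 and 0.02), and power then rises with ICC (88.5% at 0.05, 90.1% at 0.10). No analysis loses power as ICC grows.

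**5. The planned contrast.** The group × time effect compares changes from baseline, and a time-constant hospital intercept is in both measurements and subtracts out. With a change SD of 0.24/0.56 = 0.43, simulated power was 89.0%, 90.3%, 89.4% and 90.2% for hospital intercept SDs of 0, 0.2, 0.5 and 1.0 z-score units. An ICC in handgrip level thus has no effect on this contrast. An ICC in change is the case covered in step 4.

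**6. What could cost power.** Suppose the treatment effect varies between hospitals with SD τ, in units of the change SD (an assumption; the documents give no value). With equal hospitals, variance ≈ 4/N + τ²/11. For τ = 0, 0.1, 0.2, 0.3 and 0.4, approximate power is 90.0%, 89.1%, 86.4%, 81.9% and 75.7%. A simulated t test whose standard error ignores this variation keeps about 85–86% at τ = 0.3, but its type I error is then about 8%. To yield design effects of 1.135, 1.27 and 1.675, τ would have to be about 0.21, 0.30 and 0.47, or 0.09, 0.13 and 0.20 z-score units after multiplying by 0.43.

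**The case against.** The best defence is that the plan discloses what it did. It states the formula, says the trial is not cluster-randomised, says the ICC is unknown and calls the analysis conservative. The design power of 89.6% is given separately and is right, so the lower figures can be read as a pessimistic bound. Nothing is built on them: the target of 158 comes from 134/0.85. The part of the conclusion that claims more than 80% power up to ICC 0.02 is still true.

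Most of this stands, and it limits the weight of the point. It does not cover the closing clause, which presents loss of power with greater clustering as a property of this trial. Nor does it explain the ICC 0.02 threshold, which exists only because of the formula.

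A second defence is that hospitals do differ: section 2.12 says routine care will not be standardised across sites, and the Discussion expects site-level heterogeneity. That could make the treatment effect vary and so cost power. But it is a different quantity from the hospital ICC. Section 2.4 does not invoke it and the model in section 2.15 has no term for it.

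Three stronger readings are tempting and are not supported. The figures are not miscalculated, because they follow from the stated formula. The trial is not shown to be under-powered or wrongly sized, because the error runs the other way. And no recruitment decision is shown to depend on the ICC: sections 2.4 and 2.15 attach no rule to it, and enrolment beyond target to 30 September 2026 is a general policy.

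**Conclusion.** The point holds as an error in the choice of method. The effective sample sizes of 120/107/81, the powers of 86/82/70% and the statement that greater clustering reduces power do not describe this trial. Under individual allocation within hospitals, power is about 89–91% over ICC 0 to 0.10, so the plan understates it by about 4 points at ICC 0.01, 7–8 at 0.02 and 20 at 0.05.

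This rests on d = 0.56, 134 evaluable participants, allocation as in section 2.5, and a treatment effect common to all hospitals. A reader might infer that power is about 90% whatever happens between hospitals. The documents do not support that either, because variation in the effect would lower it. The consequence is confined to how the trial's power is described. Sample size, randomisation and the primary analysis are unaffected.

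**What to change.** In section 2.4, delete the design-effect calculation and the clause that greater clustering reduces power. Put in its place a statement that participants are individually randomised within hospitals and that, assuming a treatment effect common to all hospitals, the hospital ICC does not materially reduce the stated power of about 90%.

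If a pessimistic scenario is wanted, present it as between-hospital variation in the treatment effect, with the assumed SD stated and labelled as an assumption, and not as a hospital ICC.

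The cost is a few sentences of protocol text, with no change to sample size, design or analysis.

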Current recommendations support regular muscle-strengthening activities for children and adolescents with type 1 diabetes (20), whereas consensus statements emphasize that exercise benefits require individualized planning because glycemic responses vary by insulin availability, carbohydrate intake, technology use, and exercise characteristics (11, 29). This rationale is biologically plausible because skeletal muscle is a major metabolically active and endocrine tissue that secretes myokines involved in substrate oxidation, inflammation, angiogenesis, extracellular-matrix remodeling, and inter-organ crosstalk, while muscle contraction activates insulin-independent glucose uptake through GLUT-4 translocation and AMP-activated protein kinase pathways that may persist for several hours after exercise (76, 77). Prior randomized evidence suggests that exercise training can improve glycemic stability in youth with type 1 diabetes, but the literature remains heterogeneous regarding exercise type, duration, intensity, supervision, and implementation context, particularly for resistance-focused interventions (22). Diactive-1 has previously shown high usability and favorable single-center effects on insulin requirements, glycemic stability, muscular strength, lean mass, and bone-related outcomes, but those findings do not establish transportability across heterogeneous clinical settings, technologies, and participant profiles (10, 24). The present scale-up trial therefore has value primarily as an external-validity and implementation test of a refined intervention model rather than as a mere replication of the original RCT.

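### The eligibility rules admit youth from the earlier Navarre Diactive-1 trial at the Pamplona site, and nothing in the stated plan would identify them in the analysis

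*Protocol article*

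**What the plan says.** Section 2.3 gives an explicit eligibility list. The inclusion rule opens with "This study will include children and adolescents aged 10 to 18 years with a diagnosis of type 1 diabetes mellitus" and adds clinical, technology, consent and language conditions. The exclusions begin with "presence of comorbidities that limit the ability to perform physical activity during the study period"; the other two are lack of a compatible device and lack of internet. None concerns earlier participation in a Diactive-1 study or earlier use of the app, and no washout is given. Section 2.4 then states that "All individuals meeting the inclusion criteria will be eligible to participate to minimize selection bias".

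The Introduction describes "Our previous randomized clinical trial (RCT) conducted in Navarre, Spain, involving 62 youth with type 1 diabetes" and reports gains in muscular strength in it. Section 2.1 lists a Pamplona (Navarra) hospital among the eleven recruiting units. Section 2.4 takes the planning effect for handgrip z-score (0.24 units, d = 0.56) from that earlier trial.

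Of the earlier trial's results, the Discussion says that "those findings do not establish transportability across heterogeneous clinical settings, technologies, and participant profiles". It presents the new trial's value as mainly a test of external validity and implementation.

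**The concern.** Read together, these sections let a young person who trained with Diactive-1 in the first trial be screened in Pamplona, found eligible and randomized again. Two things are at stake.

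- **Size of the contrast.** A former user allocated to the app a second time may already have made part of the strength gain that the Introduction reports. Less further change from baseline in such participants would shrink the between-group difference.
- **Purpose of the trial.** The case for scaling up is that one clinical context and a limited sample do not show that the program works elsewhere. Re-enrolling members of the sample that produced the planning effect works against that aim at the site concerned. Returning volunteers are also a selected group for the usability and engagement outcomes.

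The plan as described could not detect either problem, because prior exposure appears nowhere among the variables it lists.

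**Working it through.** **1. Can former participants enter, and would they be seen?**

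| Place in the protocol article | What it fixes | Prior Diactive-1 exposure mentioned? |
|---|---|---|
| 2.3 Eligibility | Inclusion list and three exclusions | No |
| 2.4 Recruitment | All who meet the inclusion criteria are eligible | No |
| 2.5 Randomization | Central, non-stratified | No |
| 2.10.3 and 2.10.10 | Clinical and sociodemographic variables | No |
| 2.15 Primary model | Group, time, group × time; random intercepts for hospital and participant; no other covariates | No |
| 2.15 Effect modifiers | Sex, pubertal status, insulin delivery, insulin type, CGM system | No |

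They can enter, and nothing listed would identify them.

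**2. The plan's own figure.** Inputs from section 2.4: d = 0.56, 67 evaluable per group, two-sided α = 0.05. The noncentrality is 0.56 × √(67/2) = 3.24 on 132 degrees of freedom, which gives power of 89.6%, as stated. Attrition: 134 / 0.85 = 157.6, rounded up to 158, as stated. Neither figure is in dispute.

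**3. Illustrative dilution.** Let k be the number of former app users among the 158 and r the share of the full effect that they still show. Assume that they are split evenly between arms, drop out like everyone else and leave the SD unchanged. Then

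d_eff = 0.56 × [1 − (k/158)(1 − r)]

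The documents give neither k nor r. The one planning figure that helps to bound k is the mean hospital size of about 14.5 in section 2.4, together with the single Navarra site in section 2.1. For k = 14.5, k/158 = 0.092.

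| k | r | d_eff | Difference (z-score) | Power, 67 per group |
|---|---|---|---|---|
| 0 | – | 0.56 | 0.24 | 89.6% |
| 5 | 0 | 0.54 | 0.232 | 87.6% |
| 5 | 0.5 | 0.55 | 0.236 | 88.6% |
| 10 | 0 | 0.52 | 0.225 | 85.4% |
| 10 | 0.5 | 0.54 | 0.232 | 87.6% |
| 14.5 | 0 | 0.51 | 0.218 | 83.2% |
| 14.5 | 0.5 | 0.53 | 0.229 | 86.7% |

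The k = 14.5 rows treat every recruit at an average-sized Navarra site as a former app user, which is a severe assumption. If the Pamplona unit recruits more than the average, k could be larger; the documents do not say.

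**The case against.** The case against making much of this is strong in several respects.

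- **Randomization.** Allocation is individual, so former users are balanced between arms in expectation. There is no confounding, and having contributed to the planning effect does not bias a new randomized comparison. This stands.
- **Contaminated usual care.** A reader might infer that a former user in usual care spoils the comparator. The documents do not support that. The primary effect is the difference in change from baseline (section 2.15), so strength gained before baseline already sits in the baseline value. Contamination would need continued use of the app during follow-up, which is nowhere stated, and any loss of earlier gains in usual care would widen the contrast.
- **Number affected.** A reader might also take all 62 (39% of 158) as the exposed pool. That does not follow. The earlier trial compared the app with usual care, so not all 62 were allocated to the app, and the documents do not say whether its controls received it later. Nor do they say how many are still aged 10 to 18 and otherwise eligible, or that the earlier trial used this hospital. Totals well above 14.5 would need more former users than an average site recruits altogether.
- **Direction.** Version 2.0 has an updated algorithm, and its programs are set by baseline percentile with progressive overload. Further gain is therefore plausible, and former users might adhere better. No further effect is the extreme case.
- **External validity.** Ten of the eleven hospitals lie outside Navarra, and open eligibility is a stated choice to limit selection bias.

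These arguments limit the size of the problem. They do not answer the point that the written rule admits former users and the plan could not find them afterwards. Eligibility is spelled out in the article, so this is not a detail left to a fuller document.

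**Conclusion.** The point holds in a limited form. Sections 2.3 and 2.4 admit participants from the earlier Navarre trial at one of eleven sites, and no listed variable, stratum or model term identifies them. The consequences are a possible dilution of the primary contrast and a weaker external-validity claim at that site; confounding is not among them.

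The size of the dilution cannot be derived from the documents. With one average-sized site made up entirely of former users, power falls from 89.6% to about 83% if they show no further effect, or about 87% if they show half of it. Smaller numbers of former users cost less. These figures rest on assumed values of k and r, and the direction is likely rather than certain.

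**What to change.** Add a fourth exclusion to section 2.3: participation in an earlier Diactive-1 trial, or previous use of any version of the Diactive-1 app. Check it at screening by asking the family and, at the Navarra site, against the earlier trial's participant list.

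If such participants have already been randomized, or if the sponsor prefers to keep eligibility open, record prior Diactive-1 exposure as a baseline variable (earlier arm and any later app use). Keep these participants in the intention-to-treat analysis, and prespecify a sensitivity analysis of the primary outcome without them. The protocol should state which course it takes.

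The cost is a small amendment, one screening question and a slightly smaller recruitment pool at one of eleven hospitals. The planned sample size of 158 and the stated power do not change.
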